### Assessment of secondary endpoints

#### Objective physiological measures

##### Cardiorespiratory fitness

The patients’ cardiorespiratory fitness is assessed by an incremental maximum work test on a bicycle ergometer as described by Andersen et al [40]. The test is modified to accommodate the patients’ fitness level in order to obtain a test period of 5 minutes or more. Following a 5-minute warm-up period on individual steady state work intensity the work load increases by 20 watt each minute until exhaustion is reached. Maximum work load (Watt), maximum heart rate (beats per minute) and time to exhaustion are recorded as test results. This test has been shown in previous studies to be suitable when estimating cardiorespiratory fitness in patients with chronic disease [41].

#### Plasma

C-reactive protein (CRP) and hemoglobin are assessed at baseline and at the end of the intervention. If Anti-CCP and IgM rheumatoid factor are not available these blood samples will also be taken. In addition, blood pressure, weight and height will be measured.

#### Disease activity

Disease Activity Score (DAS28) is calculated from the number of swollen and tender joints (28 joints), CRP and the patients’ global assessment of how much arthritis affects their lives.

##### Patient reported outcomes

The trial includes six standardized validated questionnaires assessing changes in patient-reported outcomes.

#### Sleep quality and sleep disturbances

The Pittsburgh Sleep Quality Index (PSQI) [42] measures self-reported sleep quality and disturbances during the previous four weeks. PSQI has 19 items and measures 7 components of sleep: subjective sleep quality, sleep latency, sleep duration, sleep disturbance, use of sleeping medication, habitual sleep efficiency and daytime dysfunction.

#### Sleepiness

The Epworth Sleepiness Scale (ESS) [43] is a self-reported questionnaire that measures daytime sleepiness. The questionnaire consists of 8 items with a respondents format 0 = would never doze, 1 = slight chance of dozing, 2 = moderate chance of dozing, and 3 = high chance of dozing.

#### Sleep pattern

Patients complete sleep diaries for 14 days after each PSG measurement in order to monitor and describe potential changes in their sleep. The sleep diary contains self-reported information about what time they go to bed and get up, as well as the number of awakenings during the night and daytime dysfunction.

#### Fatigue

The Bristol Rheumatoid Arthritis Fatigue Multi-Dimensional Questionnaire (BRAF MDQ) [44] consists of 20 items including four sub-scale scores of physical fatigue, living with fatigue, cognitive fatigue and emotional fatigue. The questionnaire consists of four options; “not at all”, “a little”, “quite a bit”, “very much”.

#### Depression

The Center for Epidemiological Studies-Depression (CES-D) [45] consists of 20 items evaluating depressive symptomatology and attitudes. The patients indicate how often, over the previous week, they had experienced each of the 20 symptoms on a scale ranging from 0 to 3: rarely or none of the time; some or a little of the time; occasionally or a moderate amount of the time; most or all of the time.

#### Physical function

The Health Assessment Questionnaire (HAQ) [46], includes 20 items to assess activity limitation in 8 dimensions of activities of daily living: dressing and grooming, arising, eating, walking, hygiene, reach, grip, and common daily activities. In addition, in the HAQ questionnaire there is also a Visual Analogue Scale (VAS) for pain, fatigue and patient global assessment indicating how much arthritis affects their lives.

#### Health-related quality of life

EuroQol (EQ-5D-5 L) [47] measures health-related quality of life. The questionnaire contains five dimensions: mobility, self-care, usual activities, pain/discomfort and depression/anxiety. Each dimension has five levels: ‘no problems’, ‘slight problems’, ‘moderate problems’, ‘severe problems’ and ‘extreme problems’.

#### Health status and behavior

Information about self-reported co-morbidity, age, gender, education, work, income, physical activity, smoking, alcohol and caffeinated drink consumption is recorded. Patients are also asked for information about current medical treatment.

### Statistical analyses

Continuous variables, i.e., sleep, cardiorespiratory fitness, physical function, pain, fatigue, depressive symptoms and health-related quality of life will be presented as either means with corresponding 95% confidence limits or as medians and interquartile range (IQR). The primary and secondary endpoints will be reported as a two-sample t-test comparing change scores in the two randomized groups. The primary outcome variables in the regression model will be sleep parameters. The regression model will allow control for the baseline value of the trial endpoints and other confounding variables that may impact changes in sleep parameters (e.g. age and gender). Categorical data, i.e., single questionnaire items, will be reported as proportions and compared across randomized groups using chi-squared tests or logistic regression. Significance level will be set at 0.05. All tests will be two-tailed. The primary analysis will compare changes in the intervention vs. the control group using the intention-to-treat principle including all available data. Missing observations will be handled according to the missing at random assumption. The secondary analysis will include only patients attending at least 14 exercise sessions (80%) out of the prescribed 18 (i.e. per protocol analysis). Finally, correlations will be performed to examine the dose-response relation between changes in the primary outcome (sleep) and cardiorespiratory fitness. Data entry will be undertaken using a secure web server and statistical analysis will be performed using Statistical Analysis Systems (SAS) version 9.3.

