#### Sample size

The sample size calculation is based on the sleep component `sleep efficiency´. A previous RCT [37], using PSG as measurement of sleep, examined the effect of a non-pharmacological intervention (cognitive behavioral therapy) on sleep disturbances in patients with insomnia and found a mean sleep efficiency of 81.4% (SD 7.4). The normal value for sleep efficiency is >85%. Thus the aim for the patients in the exercise intervention was to achieve a sleep efficiency of at least 86%. On this basis, and with a significance level of α = 5% and a power of 80%, it is estimated that 36 patients should take part in this trial. A drop-out rate of 20% is expected, which means that 44 patients are included, of which 22 are randomly assigned to the intervention group and 22 to the control group.

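### The primary outcome is given both a change-score t-test and a baseline-adjusted regression, without saying which decides; if the t-test does, precision is lost unless baseline and follow-up are highly correlated

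*Protocol article*

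**What the plan says.** Under Statistical analyses, the protocol article first states that "The primary and secondary endpoints will be reported as a two-sample t-test comparing change scores in the two randomized groups". The next sentences bring in a regression model whose primary outcome variables are sleep parameters, and say that "The regression model will allow control for the baseline value of the trial endpoints and other confounding variables", with age and gender as examples only.

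The sentence in that section that opens by naming the primary analysis fixes the contrast (changes, intervention against control) and the analysis set (intention to treat, all available data). It does not fix the model. Neither analysis is called supportive or a sensitivity analysis. On error rates the section says "Significance level will be set at 0.05" and "All tests will be two-tailed".

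The Sample size section works from sleep efficiency, "with a significance level of α = 5% and a power of 80" per cent, and concludes that "it is estimated that 36 patients should take part in this trial". It mentions neither the t-test nor the regression, and gives no correlation between baseline and follow-up.

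**The concern.** Two analyses of the same outcome can give different estimates and different p-values. If neither is named as decisive, the choice can be made after the results are seen, and the stated 5% level then no longer describes the procedure. The open covariate list adds further candidate models.

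Precision is also at stake. An unadjusted comparison of changes subtracts the whole baseline value. When r is below 1 this over-corrects for a chance baseline difference and carries extra noise. ANCOVA estimates how much of the baseline to remove. With about 18 to 22 patients per arm the difference can matter, and the baseline polysomnography value it needs is collected anyway.

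**Working it through.** **Inputs.** The difference is 86 − 81.4 = 4.6 points and the SD is 7.4 (Sample size). The level is two-sided 5% (Statistical analyses). There are 36 evaluable patients, so 18 per arm (Sample size). The correlation r is not given and is assumed over a range. The SD of 7.4 is the SD of a level, not of a change, and is assumed equal at both visits.

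**The plan's own figure.** For two means, n per arm = 2 × (1.960 + 0.842)² × 7.4² / 4.6² = 2 × 7.85 × 54.76 / 21.16 ≈ 40.6, rounded up to 41, or 82 in total. The stated 36 is not reproduced. That is a separate point. Here it matters only because it shows there is little power to give away.

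**Formulas.**
- SD of change = 7.4 × √(2(1 − r))
- Residual SD under ANCOVA = 7.4 × √(1 − r²)
- Variance ratio, ANCOVA to change score = (1 − r²) / (2(1 − r)) = (1 + r)/2
- Standard error of the difference = SD × √(2/18) = SD/3

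| r | SD of change (SE) | ANCOVA SD (SE) | Variance ratio | Power by noncentral t: t-test / ANCOVA |
|---|---|---|---|---|
| 0.3 | 8.76 (2.92) | 7.06 (2.35) | 0.65 | 33% / 48% |
| 0.5 | 7.40 (2.47) | 6.41 (2.14) | 0.75 | 44% / 55% |
| 0.7 | 5.73 (1.91) | 5.28 (1.76) | 0.85 | 65% / 72% |
| 0.85 | 4.05 (1.35) | 3.90 (1.30) | 0.925 | 91% / 93% |

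**Cost of estimating slopes.** The formulas treat the baseline slope as known. Simulation with 18 per arm charges for estimating it. The last column adds age and sex, assumed unrelated to outcome.

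| r | t-test on change | ANCOVA, baseline only | ANCOVA, baseline + age + sex |
|---|---|---|---|
| 0.3 | 34% | 47% | 44% |
| 0.5 | 45% | 54% | 52% |
| 0.7 | 65% | 71% | 68% |
| 0.85 | 91% | 92% | 90–91% |

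The gain from baseline adjustment is therefore about 13, 9, 6 and 1 percentage points. With two uninformative covariates it is about 10, 7, 3 and none. Covariates that do predict outcome would improve on the last column.

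**Choosing between analyses.** In 20,000 simulated null trials per value of r (18 per arm, r = 0.3 to 0.7), each analysis alone rejects in about 5%. Taking the smaller p-value of the t-test and the baseline ANCOVA rejects in about 7–8%. Letting the model with age and sex compete as well gives about 7–9%.

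**The case against.** The strongest reply is that the text can be read with a clear order. The primary outcome is described as a change, the t-test is how endpoints are to be reported, and the regression is introduced permissively as something that allows control for covariates. On that reading the t-test is primary and the regression is adjusted support. This is a natural reading, and it is why the point is not put as two rival primary tests. But the article never states that order, and it attaches the primary outcome to the regression by name. If the order is as suggested, the less precise analysis decides, so the precision point remains.

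Second, a condensed article may leave the exact covariate list to an analysis plan that is not shown. This is fair, and the open list alone would be no finding. It counts here only because it sits beside an unranked pair of analyses.

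Third, the change-score t-test is valid. This stands: randomisation makes it unbiased, and its simulated type I error is about 5%. A reader might also infer that its variance can never be below that of ANCOVA. The large-sample ratio (1 + r)/2 suggests so, but in a trial this small, at high r and with extra uninformative covariates, the adjusted model can be no better or slightly worse.

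Fourth, the type I inflation arises only if someone selects on the p-value. Nothing in the article says that this is intended.

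**Conclusion.** The point holds in a limited form. The article attaches two analyses to the primary outcome and does not say which gives the primary result. If the t-test decides, as its wording suggests, the trial gives up about 13 points of power at r = 0.3, 9 at 0.5 and 6 at 0.7 against ANCOVA on baseline alone, and almost nothing at r = 0.85. These sizes rest on equal SDs of 7.4, a 4.6-point difference, 18 evaluable per arm and an assumed r. The direction is secure at low and moderate r; the size is not known.

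A reader might infer that adopting ANCOVA would restore the planned 80% power. The figures do not support that: by the large-sample formula, with 36 evaluable patients it needs r of about 0.75, against about 0.78 for the t-test. The shortfall in sample size is a separate matter. The trial can be analysed either way. What is missing is a fixed decision, and the more precise option is available from data already planned.

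**What to change.** Before outcome data are analysed, name one primary analysis: a linear regression of the end-of-intervention value of the primary sleep parameter on randomised group and its own baseline value. List any further covariates in advance, or state that there are none. Report the adjusted difference with its 95% confidence interval, and make the change-score t-test a sensitivity analysis.

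The investigators should state which parameter this is. Sleep efficiency is the one the trial is sized on, but the analysis text speaks of sleep parameters in the plural. For continuous secondary endpoints, use the same baseline-adjusted approach where a linear model is suitable. The section already expects that some variables will be summarised by medians, so one model need not be imposed on all of them.

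The cost is a few sentences of text and one or a few degrees of freedom. No new data are needed. The Trial status section says that recruitment was still under way at submission.

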Against this background, the aim of this trial is to assess the efficacy of an aerobic intermittent exercise training intervention on sleep quality and sleep disturbances in patients with RA. The primary hypothesis is that intermittent aerobic exercise will be superior to no exercise in the improvement of objectively measured sleep. The secondary hypotheses are that patients randomly assigned to the exercise intervention will show greater improvement in subjective sleep quality and sleep disturbances, cardiorespiratory fitness, and physical function as well as reduced pain, fatigue and depressive symptoms and improved health-related quality of life compared to patients randomly assigned to the no-intervention (control group).

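### Single questionnaire items, neither named nor limited in number, are to be tested between arms at an unadjusted 0.05 alongside the scale scores

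*Protocol article*

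**What the plan says.** The Statistical analyses section deals with patient-reported data in two ways.

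- **Scale level.** Physical function, pain, fatigue, depressive symptoms and health-related quality of life are listed as continuous variables. Primary and secondary endpoints are compared by two-sample t-tests on change scores. A regression model that can control for baseline is also described, with sleep parameters as its outcome.
- **Item level.** "Categorical data, i.e., single questionnaire items, will be reported as proportions and compared across randomized groups using chi-squared tests or logistic regression".

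One threshold covers everything: "Significance level will be set at 0.05. All tests will be two-tailed".

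Under Patient reported outcomes the article says: "The trial includes six standardized validated questionnaires assessing changes in patient-reported outcomes". The hypotheses at the end of the Background are about constructs. They begin "The secondary hypotheses are that patients randomly assigned to the exercise intervention will show greater improvement in subjective sleep quality and sleep disturbances" and go on to fitness, physical function, pain, fatigue, depressive symptoms and quality of life.

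**The concern.** The item sentence fixes the unit of analysis, the comparison, the type of test and, with the sentence on significance, the threshold. It does not say which items are meant or how many, and it gives them no lower standing than the scale scores. A long run of item tests at 0.05 will tend to produce some significant results by chance.

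Three features of the trial make such results easy to over-read:

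- **Patients know their arm.** Only the polysomnography technicians are described as blinded, and controls receive no exercise. Self-reported answers are therefore open to expectation effects.
- **The trial is small.** There are 22 patients per arm, or about 18 after the expected drop-out, so item tables are sparse.
- **The item tests answer no stated question.** Every secondary hypothesis concerns a construct. One significant fatigue or depression item could be presented as support for a hypothesis that the scale score does not support.

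**Working it through.** The article gives no total item count, expected number of false positives or familywise error rate, so there is no figure of its own to reproduce here. All inputs except those marked as assumptions come from the article.

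**Step 1: how many items are collected.**

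| Questionnaire (section) | Items | Response levels stated |
|---|---|---|
| PSQI (Sleep quality and sleep disturbances) | 19 | not stated |
| ESS (Sleepiness) | 8 | 4 |
| BRAF MDQ (Fatigue) | 20 | 4 |
| CES-D (Depression) | 20 | 4 |
| HAQ (Physical function) | 20 | not stated |
| EQ-5D-5L (Health-related quality of life) | 5 | 5 |

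Total: 19 + 8 + 20 + 20 + 20 + 5 = 92. The three visual analogue scales attached to the HAQ are extra and are not counted. The article does not say that all 92 items will be tested, so 92 is an upper limit for one round of testing.

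**Step 2: expected false positives if no item has a true effect.** The mean is k × 0.05 for k items tested at nominal size, and it does not require independence. The chance of at least one is 1 − 0.95^k, which does require independence. The smaller values of k are assumptions; 73 is all items except the PSQI (92 − 19).

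| k | k × 0.05 | 1 − 0.95^k |
|---|---|---|
| 20 | 1.0 | 64% |
| 40 | 2.0 | 87% |
| 73 | 3.65 | 98% |
| 92 | 4.6 | 99.1% |

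**Step 3: allowing for correlation.** Items of one scale measure the same thing and are not independent. This was simulated with 92 equally correlated normal test statistics and 20,000 replicates. The correlations are assumptions.

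| Correlation | Mean count | Median | 5th–95th percentile | At least one |
|---|---|---|---|---|
| 0 | 4.6 | 4 | 1–8 | 99% |
| 0.3 | 4.6 | 3 | 0–14 | 93% |
| 0.5 | 4.6 | 2 | 0–19 | 76% |

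The mean does not move. Correlation makes it more likely that there are none, and also more likely that there are many.

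**Step 4: cell sizes.** The Sample size section gives 22 randomized per arm and 36 evaluable patients, so 18 per arm. Average patients per cell:

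- four levels: 22/4 = 5.5 and 18/4 = 4.5
- five levels: 22/5 = 4.4 and 18/5 = 3.6

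Skewed answers would make some cells smaller.

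**Step 5: what sparse cells do to the chi-squared test.** Uncorrected tests were simulated with no true difference (4,000 tables per setting) under assumed response distributions with two to five levels. Actual size ran from 2.7% to 6.2%. The 6.2% came from a two-level item split evenly at 18 per arm. The four- and five-level settings all lay between 2.7% and 4.6%. Over 92 items, the full range corresponds to about 2.5 to 5.7 expected false positives.

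**The case against.** **The scale scores are analysed.** A reader might infer that item testing bypasses the validated scores. The documents do not support that: the same section analyses these domains as continuous variables with t-tests on change. The item tests are additional. This objection stands.

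**The number of tests is not stated.** The item sentence can be read as a rule for a data type and not as a list of tests. It might be applied only to selected items. This also stands, so 92 and 4.6 are upper limits and not a forecast. It does not remove the point, because the article states the comparison and the threshold without any limit.

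**Chance findings are not certain.** The 99% figure needs 92 independent tests. Under the assumed correlations the chance of at least one is 76% to 93%, and sparse four- and five-level tables lower the test size. Describing isolated significant items as almost certain would be too strong.

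**Logistic regression is one of the two options.** It could adjust for the baseline answer and, in ordinal form, respect the order of the responses. It therefore cannot be said that the plan must ignore both. A chi-squared test does ignore both, however, and the item sentence promises neither adjustment nor an ordinal model.

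**This is detail for an analysis plan.** The choice of items, the grouping of levels and any multiplicity rule can properly be left to a document not shown, and their absence is not criticised here. The point concerns the testing rule that the article does state.

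**The fix leaves multiplicity.** It does. One score for each of six instruments plus three visual analogue scales makes nine, and 9 × 0.05 = 0.45 expected false positives, against up to 4.6 from items. These nine are the intended measures of their constructs; the single items are not.

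**Conclusion.** The point holds in limited form. The article plans between-arm tests of an unlimited and unnamed set of single items at an unadjusted two-sided 0.05, in addition to the scale-score analyses, and no secondary hypothesis calls for them.

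The size is up to about 4.6 false positives on average. That figure assumes no true effect on any item, all 92 items tested once, and tests at nominal size. It falls to about 2 for 40 items and 1 for 20. Correlation between items makes the realised count highly variable, and sparse tables make the chi-squared test an uncertain tool for the multi-level items.

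The consequence is confined to how secondary patient-reported results are read. The primary outcome, sleep measured by polysomnography, is untouched. The wording is worth correcting, but it does not threaten the trial's main conclusion.

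**What to change.** Replace the item sentence in Statistical analyses with a statement that:

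- single questionnaire items will be reported descriptively, as counts and proportions by arm and visit, without between-arm p-values, and no conclusions will be drawn from them;
- inference on patient-reported outcomes will rest on the instrument scores tied to the secondary hypotheses, each compared between arms with adjustment for its baseline value. The candidates are the scores of the PSQI, ESS, BRAF MDQ, CES-D, HAQ and EQ-5D, and the visual analogue scales.

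The data are already collected at baseline and at the end of the intervention, and the section already describes a regression model that can control for baseline. The cost is a change of wording and the loss of item-level p-values; there is less analysis to run.

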#### Trial endpoints

##### Data collection

Objective physiological as well as patient reported outcomes are collected at baseline and at the end of the intervention (6- 8 weeks).

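### Ordered questionnaire items are to be compared by chi-squared or an unspecified logistic regression; no analysis that uses both the order and the baseline answer is fixed (minor, item-level analyses only)

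*Protocol article*

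**What the plan says.** The analysis of single items is set in one sentence of the protocol article, under Statistical analyses. It labels them categorical data and states that "single questionnaire items, will be reported as proportions and compared across randomized groups using chi-squared tests or logistic regression". The same section adds "Significance level will be set at 0.05" and "All tests will be two-tailed".

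The items are ordered:
- **Sleepiness (ESS):** 0 to 3, from no chance to a high chance of dozing.
- **Fatigue (BRAF MDQ):** four graded answers.
- **Depression (CES-D):** patients report how often they had "experienced each of the 20 symptoms on a scale ranging from 0 to 3".
- **Health-related quality of life (EQ-5D-5L):** "Each dimension has five levels", running from no problems to extreme problems.

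Under Data collection, "patient reported outcomes are collected at baseline and at the end of the intervention", so each item has a baseline answer. The regression paragraph allows control for baseline values of trial endpoints, but does not tie this to single items. The outcome constructs themselves (sleep, function, pain, fatigue, depressive symptoms, quality of life) are treated as continuous and compared on change scores.

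**The concern.** Chi-squared is named as one of two ways to compare ordered answers. On a table of two arms by four or five levels it spends 3 or 4 degrees of freedom and gives the same result if the levels are shuffled. It also leaves out each patient's baseline answer. With about 20 patients per arm, a consistent shift toward better answers can be missed by this test when the same data would show it under an ordinal analysis.

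The other named option, logistic regression, is not specified. In its binary form the result depends on where the answers are split, and no split is given. In its ordinal form, with baseline as a covariate, the problem disappears. The sentence thus leaves open a choice between methods of quite different power.

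**Working it through.** **Inputs from the article.** Two-sided 5% level (Statistical analyses). 22 patients per arm (Randomization and blinding). 36 evaluable patients, or 36/2 = 18 per arm (Sample size). Four or five levels per item. The article states no power, effect or answer distribution for single items, so there is no plan figure to reproduce on this point. The figure of 36 was derived for sleep efficiency and serves here only as a size.

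**Step 1: sparseness.** Mean expected count = patients / (2 × levels).
- Five levels: 44/10 = 4.4; 36/10 = 3.6.
- Four levels: 44/8 = 5.5; 36/8 = 4.5.

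Where the mean is below 5, at least one cell must be below 5. For four levels and all 44 patients, every cell can reach 5 only if each level holds at least 10 of the 44 answers.

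**Step 2: power by simulation.** Assumptions, none from the article: a latent normal item cut into 4 or 5 levels (even, mid-peaked or skewed), baseline to follow-up correlation 0.5 or 0.7, and a shift of 0.6, 0.8 or 1.0 SD. There were 3,000 runs per scenario (standard error at most √(0.25/3000) ≈ 0.009). Proportional-odds fits used 400 runs (at most √(0.25/400) = 0.025). Results at 0.8 SD and correlation 0.5:

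| Per arm, item | Chi-squared | Wilcoxon | Rank ANCOVA with baseline | Proportional odds with baseline |
|---|---|---|---|---|
| 18, 4 even levels | 0.38 | 0.56 | 0.63 | 0.66 |
| 18, 5 mid-peaked | 0.34 | 0.61 | 0.69 | 0.72 |
| 22, 4 even levels | 0.48 | 0.66 | 0.73 | 0.78 |
| 22, 5 mid-peaked (400 runs throughout) | 0.40 | 0.72 | 0.78 | 0.81 |

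Relative loss = 1 − chi-squared power / comparator power. For the first row it is 1 − 0.38/0.63 = 40% against the baseline-adjusted rank analysis, and 1 − 0.38/0.56 = 32% against Wilcoxon, which isolates the order. For the second row the figures are 51% and 44%.

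**Step 3: range.** Over 50 non-null scenarios the ratio of chi-squared to baseline-adjusted power was 0.32 to 0.76 (median 0.53), a loss of 24 to 68% (median 47%). From order alone the ratio was 0.46 to 0.81 (median 0.62), a loss of 19 to 54%. A further simulation at 18 to 22 per arm gave 19 to 64%, and 16 to 52% from order alone. With a very large assumed effect (1.2 SD, correlation 0.3, 22 per arm, four levels) the loss fell to 1 − 0.83/0.95 = 13%. The 50 scenarios do not include five-level items at 22 per arm. Those were covered only by the 400-run check, with ratios to proportional odds of 0.44 to 0.51.

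**Step 4: type I error.** Chi-squared rejected 3 to 5% of the time under no effect, although 90 to 100% of tables had more than a fifth of expected counts below 5.

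**Step 5: dichotomising.** At 18 per arm, with an assumed cumulative odds ratio of 4 and level shares of 35/30/20/10/5%, an unadjusted two-group test had power 0.58, 0.37, 0.15 or 0.01 depending on the cut. The lowest value comes from isolating the level assumed to hold 5% of answers. Binary logistic regression at a median split with baseline did better. In the four scenarios of the table, in order, its power was 0.50, 0.48, 0.62 and 0.54, still below proportional odds.

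**The case against.** The strongest reply is that the sentence offers logistic regression as an alternative. That can be a cumulative-logit model with the baseline answer as covariate, which is the remedy itself. Which form is meant, how levels are grouped and what happens with sparse cells are details that a journal article commonly leaves to the full protocol or analysis plan. This stands in part: the missing details alone would be no finding. What remains is that chi-squared is named, without qualification, as an acceptable test for ordered items.

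A reader might infer that the plan commits to an unordered comparison. It does not; the article never uses that word, and ordinal regression is within its terms. A reader might also infer that a cut-point will be picked after the data are seen. Nothing in the article mentions dichotomising, so the step 5 figures show only how much a cut could matter.

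The reply that single items carry no stated hypothesis also stands. The constructs in the hypotheses are analysed as scales on change scores, which use baseline. Finally, sparse cells do not make the test invalid here, since its type I error stayed at or below about 5%.

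**Conclusion.** The point holds as a minor one. For ordered items in a trial of this size, chi-squared discards the order and the baseline answer, and the plan does not fix the one permitted option that keeps both. The cost is roughly a fifth to two thirds of the power of a baseline-adjusted ordinal analysis, and less if effects are very large. Part comes from order and part from baseline.

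That range rests wholly on assumed distributions, shifts and correlations. It would be tempting to say that half the power is lost. Half is near the middle of the simulated values, but the documents supply nothing from which to derive it, and it combines two separate losses. Nor do the documents support reading this as a threat to the trial's main conclusions, because the primary and scale-level secondary endpoints are not analysed this way.

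**What to change.** Replace the item sentence with a rule along these lines: ordered items that are analysed individually are compared by a proportional-odds logistic model with arm and the baseline item level, reporting the common odds ratio with its 95% confidence interval. If the model cannot be fitted, the single fallback is a Wilcoxon rank test stratified by baseline level. Chi-squared or Fisher's exact test is kept for nominal or binary variables. Entering the baseline level as one numeric score, as in the simulations, spares degrees of freedom in so small a sample.

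The cost is a change of wording; no further data or patients are needed. The downside is the proportional-odds assumption, which should be checked and reported.
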